### 1 month after discharge

Patients or their care givers will receive a letter by post with instructions and an assessment questionnaire for follow-up assessment at 1 month post discharge. In case of no response, the researchers will contact the patient / care giver by telephone to complete the assessment. The following items will be evaluated: **functional status** (Parker Mobility Score, Barthel Index, Lawton and Brody Scale, Katz index), **Quality of Life** (EQ-5D), **residential status**, **nutritional status**, **mortality**, **readmission** and the **presence of new falls and fractures** as well as use of calcium/vitamin D and anti-osteoporosis **medication** in a questionnaire. Only mortality and readmission will be retrospectively collected.

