# Study Synopsis

| Title of clinical trial |  | Geriatrics and traumatology co-managing fragility fractures: effectiveness and success of implementation in a single centre setting |
| --- | --- | --- |
| Protocol Short Title/Acronym |  | G-COMAN FRACTURES |
| Sponsor name |  | UZ Leuven |
| Principal Investigator |  | [name] |
| Medical condition or disease under investigation |  | Older fragility fracture patients |
| Purpose of clinical trial |  | 1) To evaluate the effectiveness of a nurse-led geriatric-traumato co-management program using outcome indicators  2) To evaluate the feasibility of a nurse-led geriatric-traumato co-management program  2.1 To evaluate the reach and fidelity  2.2 To evaluate implementation targets 2.3 To evaluate implementation determinants  3)To evaluate the process of implementation of a nurse-led geriatric-traumato co-management program  3.1 To evaluate the reach and fidelity  3.2 To evaluate process outcomes |
| Primary objective |  | 1) Effectiveness evaluation: To determine if geriatric co-management is superior in preventing in-hospital complications |
| Secondary objective (s) |  | 1) Effectiveness evaluation: To determine if geriatric co-management is superior on following outcome indicators:  - length of stay  - unplanned readmissions within 30 and 90 days  - mortality  - functional status  - nutritional status  - quality of life  - falls and new fracture rate  - Discharge to a higher care level  - secondary fracture prevention started  - Cost-benefit of G-COMAN program  2) feasibility and process evaluation: To evaluate if geriatric co-management was successful implemented on the traumato ward:  -2.1 & 3.1: reach of the program and fidelity towards the core components of the care model  - 2.2: implementation targets  - 2.3: implementation determinants  -3.2: process outcomes:  * time to start physiotherapy  * time to start dietary advice  * use and duration of physical restraints  * use and duration of indwelling catheters (urinary tract catheter or intravenous catheter)  * Medication reconciliation at admission and discharge  * referral to geriatric day clinic  * referral to fracture liaison services |
| Trial Design |  | pre-post implementation study on the traumatology ward of the University Hospitals Leuven. |

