| Endpoints |  | In-hospital complications (primary endpoint)  Length of stay, unplanned readmissions, mortality, functional status, nutritional status, quality of life, falls and new fracture rate, discharge to a higher care level, secondary fracture prevention, cost-benefit (secondary endpoints) |
| Sample Size |  | Pre-post cohort: Al least 108 patients per group  Feasibility study: 15 patients and 30 health care professionals |
| Summary of eligibility criteria |  | Pre-post cohort: Hospitalised patients aged 75 or older with a fragility fracture on the traumatology ward (E456) of the University Hospitals Leuven  Feasibility study:  - Hospitalised patients aged 75 or older with a fragility fracture on the traumatology ward (E456) of the University Hospitals Leuven  - Health care professionals of E456 will be included if they had four or more weeks of ‘full time’ experience with the programme. |
| Maximum duration of treatment of a  Subject |  | Not applicable |
| Version and date of final protocol |  | Amendment 2: 22-04-2022 |
| Version and date of protocol amendments |  |  |

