### 3.3 Secondary endpoints

1) Effectiveness evaluation

The secondary endpoints include comparison between the two groups on **patient outcome**:

- Length of hospital stay

- quality of life: EQ-5D^10^ (at admission, discharge, 1 month, 3 months, 6 months and 12 months post-surgery)

- functional status: Parker Mobility Score^11^, modified Barthel Index^12^, Lawton and Brody Scale^13^, Katz index (admission, discharge, 1 months, 3 months and 6 months post-surgery).

- hospital readmissions (30 and 90 days after discharge)

- falls (= “an unexpected event in which the patients comes to rest on the ground, floor or lower level”) and new fractures, either by retrospectively checking electronic patient record for any contact after discharge to any hospital or emergency department stating the occurrence of falls or new fractures) and by a questionnaire send out to patient and care givers. (admission, in-hospital, at discharge, at 1, 3, 6 months post-surgery 12 months post-surgery)

- Living situation: defined in 5 categories: living alone at home, living with spouse/partner, living with children, assisted living, living in a facility with 24h care such as nursing home). Details of care provided will be recorded as one of the following categories: 24h care, daily, irregular, no care. (admission, discharge, 1 month, 3 months post-surgery, 12 months after surgery)

- mortality (in-hospital, 1 month post-discharge and 12 months after discharge)

- secondary fracture prevention: documentation of fall risk assessment, medication review of calcium/vitamin D use and osteoporosis treatment, appointment to fracture liaison service (12 months after surgery)

- nutritional status: Mini Nutritional Assessment (MNA) ^14^ (at admission, 1 month, 3 months and 6 months post-surgery)

- cost-benefit analysis:

Costs will be assessed using a model that registers key hospital activities from the electronic patient record (KWS): 'beeldvorming', 'daghospitalisatie', 'dialyse', 'functiemeting', 'hospitalisatie', 'hospitalisatie ITE', 'labo', 'operatiekwartier', 'paramedische staf', 'raadpleging', 'raadpleging functiemeting', 'radiotherapie', 'spoedgevallen'. The model was developed by UHL.

2. Feasibility evaluation (is the intervention successfully implemented?):

2.1:

- the reach of the program (% of all eligible patients that were included in the G-COMAN program, defined as the patients who completed the questionnaire)

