3.6 Trial Flowchart

### *Baseline variables and effectiveness outcomes including time points in the prospective pre- and post-cohort and retrospective pre-cohort.*

| **Variable** | **Instrument** | **Description** | **Score** | **Type of assessment** | **Prospective pre-cohort/post-cohort** | | | | | | **Retrospective pre-cohort** |
| --- | --- | --- | --- | --- | --- | --- | --- | --- | --- | --- | --- |
|  |  |  |  |  | **Admission** | **Discharge** | **1M FU** | **3M FU** | **6M FU** | **12M FU** | **Yes/No** |
| Demographics | N/A | Age, gender |  | Record | X |  |  |  |  |  | Yes |
| Comorbidities | Age-adjusted Charlson Comorbidity Index | Assessment of 16 medical conditions scored based on severity and age | 0-37 | Record | X |  |  |  |  |  | Yes |
| Activities of Daily Living (ADL) | Katz index | Bathing, dressing, toileting, transferring, continence, feeding | 6-18 | Questionnaire | X | X | X | X | X |  | Only baseline via record |
|  | Modified Barthel index | Bowels, bladder, grooming, toilet use, feeding, transfers, mobility, dressing, stairs, bathing | 0-100 | Questionnaire | X | X | X | X | X |  | Only baseline via record |
| Instrumental ADL | Lawton and Brody scale | Telephone use, shopping, food preparation, housekeeping, laundry, mode of transportation, medication use, finances | 0-8 | Questionnaire | X | X | X | X | X |  | Only baseline via record |
| Nutritional status | Mini nutritional assessment | 6 screening questions | 0-14 | Questionnaire | X |  | X | X | X |  | Only baseline via record |
| Mental status | Mini-cog | Three-item word memory and clock-drawing | 0-5 | Test | X | X |  |  |  |  | Only baseline via record |
| Injury and surgery details | N/A | Type of fracture  Type of surgery  Time to surgery  ASA score |  | Record |  | X |  |  |  |  | Yes |
| In-hospital complications | N/A | Delirium  Congestive heart failure  Pneumonia  Deep venous thrombosis  Pulmonary embolism  Myocardial infarction  Urinary tract infection |  | 4AT  Record |  | X |  |  |  |  | Yes, record |
| Length of hospital stay | N/A |  |  | Record |  | X |  |  |  |  | Yes |
|  |  |  |  |  |  |  |  |  |  |  |  |
| Unplanned readmissions | N/A |  |  |  |  |  | X | X |  |  | Yes |
| Mortality | N/A |  |  | Record |  | X | X |  |  | X | Yes |
| Living situation | N/A |  |  | Questionnaire | X | X | X | X |  | X | Only baseline and discharge via record |

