# Trial Procedures

### 5.1 By visit

### Baseline assessment

All patients who were screened for the inclusion and exclusion criteria will be entered on the ‘Subject screening log’ (see appendix 1). **Demographical data** (gender, age, height and weight (to calculate the Body Mass Index), date of admission and living situation), American Society of Anaesthesiologists (ASA) physical status class^15^, comorbidities (age adjusted charlson comorbidity Index (ACCI) will be all collected by reviewing the patients’ medical record. **Functionality** (Parker Mobility Score, modified Barthel Index, Lawton and Brody Scale, Katz index), **quality of life** (EQ-5D), **fall history and residential status** will be assessed referring to the patient’s pre-injury status. **Mental status**, based on cognition, and **nutritional status** will be assessed with respectively Mini-cog and mini nutritional assessment. Details relative to the **injury** (side affected, fracture location, fracture classification), **surgery** (time to surgery, type of procedure), and total number and intake of relevant **medication** will be documented as well. All variables, except for the quality of life, can be retrospectively collected using the electronic patient record.

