### 3 months after discharge

Patients or their care givers will receive a letter by post with instructions and an assessment questionnaire for follow-up assessment at 3 months post discharge. If case of no response, the researchers will contact the patient / care giver by telephone to complete the assessment. The following items will be evaluated: **functional status** (Parker Mobility Score, Barthel Index, Lawton and Brody Scale, Katz index), **Quality of Life** (EQ-5D), **residential status**, **nutritional status**, **readmission** the **presence of new falls and fractures** as well as use of calcium/vitamin D and anti-osteoporosis **medication** in a questionnaire. Only readmission will be retrospectively collected.

Mean in-hospital costs will be calculated by UHL business manager using the UHL cost model .

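### Readmission is ascertained differently in prospective patients and retrospective controls, and is labelled unplanned in some sections but not in 3.3, so the pre-post comparison may be biased in an unknown direction

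*Protocol*

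**What the plan says.** **Source, prospective patients.** Protocol 5.1 (1 month and 3 months after discharge) describes a posted questionnaire. For non-responders at 1 month: "In case of no response, the researchers will contact the patient / care giver by telephone to complete the assessment". The 3-month text provides the same. Readmission is in the list of items at both times.

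**Source, retrospective controls.** At 1 month: "Only mortality and readmission will be retrospectively collected". At 3 months: "Only readmission will be retrospectively collected". Neither sentence names the source. The baseline text in 5.1 does so for baseline variables: "All variables, except for the quality of life, can be retrospectively collected using the electronic patient record". In the flowchart (3.6), the retrospective column likewise refers to the record wherever it names a source.

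**Flowchart.** The row "Unplanned readmissions" is marked at 1 and 3 months and answered Yes for the retrospective pre-cohort. As available, its type-of-assessment cell is empty.

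**Cohorts.** Under 3.4, the pre-cohort mixes prospectively and retrospectively collected patients because prospective recruitment will fall short. The retrospective share is not given. The post-cohort is prospective.

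**Definition.** The synopsis objective reads "unplanned readmissions within 30 and 90 days" and its endpoints row "Length of stay, unplanned readmissions, mortality, functional status". Section 3.3 reads "hospital readmissions (30 and 90 days after discharge", without the qualifier. Sections 5.1 and 8.2 speak only of readmission.

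**Analysis.** Section 8.2 treats readmission as a time-to-event outcome with death as a competing risk.

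**The concern.** A pre-post comparison of an event rate is interpretable only if events are found equally well in both periods. Here the post-cohort can be ascertained by asking the patient or caregiver, and part of the pre-cohort cannot. If the two sources differ in completeness, the observed rates will differ even when the true rates are the same. Neither the competing-risk analysis nor adjustment for baseline covariates removes an error that arises from how the event was found.

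Elsewhere the protocol does combine sources. Falls and fractures in 3.3 use both record and questionnaire, and 12-month mortality in 5.1 uses the record with a questionnaire check. Readmission has no such rule.

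The label adds a second ambiguity. All hospital readmissions and unplanned readmissions are different endpoints, and a data collector working from 3.3 could count events that one working from the synopsis would leave out.

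**Working it through.** The protocol gives no expected readmission rate, so there is no figure of its own to reproduce. Its sample size of 108 per group (8.1) concerns complications and has no bearing here.

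**Inputs, all assumed:**
- p, the true 90-day readmission rate, equal in both cohorts: 10%, 20% or 30%
- f, the retrospective share of the pre-cohort: 25%, 50% or 75%
- Sq, the share of readmissions that the questionnaire finds, and Sr, the share that the record finds: combinations between 70% and 95%

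**Formulas**, taking prospective patients as ascertained by questionnaire and retrospective ones by record:
- observed pre rate = p × [f × Sr + (1 − f) × Sq]
- observed post rate = p × Sq
- spurious difference, post minus pre = p × f × (Sq − Sr)

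**Worked case:** p = 0.20, f = 0.50, Sq = 0.95, Sr = 0.70.
- pre = 0.20 × (0.50 × 0.70 + 0.50 × 0.95) = 0.165
- post = 0.20 × 0.95 = 0.190
- difference = +2.5 points

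**Spurious difference in percentage points at p = 20%:**

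| Sq | Sr | f = 25% | f = 50% | f = 75% |
|---|---|---|---|---|
| 95% | 70% | +1.25 | +2.50 | +3.75 |
| 95% | 85% | +0.50 | +1.00 | +1.50 |
| equal | equal | 0 | 0 | 0 |
| 80% | 95% | −0.75 | −1.50 | −2.25 |
| 70% | 95% | −1.25 | −2.50 | −3.75 |

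The extremes come at p = 30% and f = 75%: 0.30 × 0.75 × (±0.25) = ±0.056, or about ±5.6 points. On 108 patients that is 0.056 × 108, about 6 patients.

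The sign is that of Sq − Sr, and the size is proportional to f. The protocol states none of these three quantities.

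**The case against.** **The questionnaire may not be the sole source for prospective patients.** The 1-month list also contains mortality, which the flowchart assigns to the record, so being listed does not exclude a record check. The flowchart cell may be empty only because the table was damaged in extraction, and the rows for length of stay and mortality both say record. If the record is in fact used for everyone, the imbalance disappears. This stands as a caution. But no text says that the record is used for everyone, and for falls and 12-month mortality, where two sources are meant, the protocol says so.

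**A reader might infer that the bias runs against the programme.** The reasoning would be that patients report admissions elsewhere which the record misses. Assuming that the record misses 10–30% of readmissions, a true rate of 20–30% and a retrospective share of 30–70%, this gives 0.2 × 0.1 × 0.3 = 0.6 points up to 0.3 × 0.3 × 0.7 = 6.3 points, always against the programme. That calculation fixes Sq at 100% and so cannot produce a negative number. The documents point both ways. Section 3.3 describes the record check for falls and fractures as reaching contacts with other hospitals and emergency departments. Section 8.2 expects questionnaire data to be lost through death, drop-out and inability to respond, and such losses would hide readmissions in the post-cohort. The directional reading is not supported.

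**A reader might also infer that dropping the qualifier inflates the post-cohort rate,** because the programme encourages infusion referrals and geriatric day-clinic visits. No section counts such contacts as readmissions. The protocol records them as referrals or appointments, and its cost model separates day hospitalisation from hospitalisation. The mechanism is conceivable but speculative.

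**The wording gap is small.** The synopsis (twice) and the flowchart carry the qualifier, and 3.3 can be read as shorthand. That is fair. It makes the correction easy, but 3.3 is where the endpoint is defined.

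**Conclusion.** The point holds as an inconsistency of source and of definition on a named secondary endpoint. As written, the plan ascertains readmission differently in part of the control group than in the post-cohort, and this can shift the comparison in either direction. The size depends on assumptions that the documents do not supply: about −5.6 to +5.6 percentage points over the ranges used, and zero if the two sources are equally complete or the record is already used for all. That retrospective readmission comes from the record alone is an inference, though the only one the text supports. The definition mismatch is a plain contradiction, with no demonstrable direction of bias. Because the sign is unknown, the bias cannot be allowed for when the result is interpreted, so it is better removed in the design. The primary endpoint is not affected.

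**What to change.** 1. In 3.3 and 5.1, name the endpoint unplanned readmission within 30 and 90 days of discharge, matching the synopsis and flowchart, and use the same term in 8.2.
2. In 3.6 and 5.1, make the electronic patient record the source for all patients, prospective and retrospective, in the main comparison. State whether it shows admissions to other hospitals.
3. Keep questionnaire-reported readmissions for prospective patients, and use events found only there in a supplementary comparison of the prospective pre-cohort with the post-cohort.

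The cost is a few lines of wording plus a record look-up for prospective patients, whose records are already consulted for other outcomes. The drawback is that readmissions not visible in the record may be under-counted. That under-count would no longer differ by collection method, although the protocol does not establish that the record is equally complete in both calendar periods.

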### 3 months after discharge

Patients or their care givers will receive a letter by post with instructions and an assessment questionnaire for follow-up assessment at 3 months post discharge. If case of no response, the researchers will contact the patient / care giver by telephone to complete the assessment. The following items will be evaluated: **functional status** (Parker Mobility Score, Barthel Index, Lawton and Brody Scale, Katz index), **Quality of Life** (EQ-5D), **residential status**, **nutritional status**, **readmission** the **presence of new falls and fractures** as well as use of calcium/vitamin D and anti-osteoporosis **medication** in a questionnaire. Only readmission will be retrospectively collected.

Mean in-hospital costs will be calculated by UHL business manager using the UHL cost model .

### 6 months after discharge

Patients or their care givers will receive a letter by post with instructions and an assessment questionnaire for follow-up assessment at 1 month post discharge. In case of no response, the researchers will contact the patient / care giver by telephone to complete the assessment. The following items will be evaluated: **functional status** (Parker Mobility Score, Barthel Index, Lawton and Brody Scale, Katz index), **Quality of Life** (EQ-5D), **nutritional status**, and the **presence of new falls and fractures** as well as the use of calcium/vitamin D and anti-osteoporosis **medication in a questionnaire**. None of the variables can be retrospectively collected.

### 12 months after admission

**Mortality** will be checked in the electronic patient record (KWS) which is linked the Federale Kruispuntbank and survival status will be double checked with patients/ care givers via questionnaire. **Quality of life** (EQ-5D) and **residential status** will also be checked in the questionnaire. Also the **presence of new falls and fractures** will be asked as well as use of calcium/vitamin D and anti-osteoporosis **medication** in a questionnaire. Only mortality will be retrospectively collected.

### Feasibility study

Before start of recruitment of the post-cohort, a feasibility evaluation in a single intervention group will be performed in order to be sure if the implementation of the intervention is delivered as intended. The feasibility of the intervention will be evaluated using a mixed-methods approach. First, the reach and fidelity (2.1) will be determined with a quantitative evaluation using the electronic patient record. The reach reflects the percentage of eligible patients that was included in the G-COMAN program. Inclusion in the program is defined as having received the questionnaire and a CGA. The number of patients who were actually included will be compared with the total number of eligible patients. The fidelity determines how well the intervention is implemented as defined by the protocol and reflects the percentages of included patients who received the core components of the intervention. Both the core components as the timing will be evaluated. The same baseline characteristics will be collected as in the pre- and post-cohort (variables at admission). Second, a survey will be sent out to all health care professionals working on the traumatology ward measuring the implementation targets (awareness, knowledge, motivation to change, perceived acceptability and feasibility, and believe in the benefit, value and success of the program) (2.2). The survey will consist of questions with each 5 response options: completely agree, agree, neutral, do not agree and completely do not agree (**appendix 3**). Thirdly, focus groups/interviews with all health care professionals will be organised to qualify the implementation barriers, namely the barriers and facilitators of the G-COMAN program (2.3). The expectations and experiences of the multidisciplinary traumatology team will be captured in a focus group/interview before start of the implementation, during the implementation and at the end of the implementation. An interview guide will be drafted to be used during the focus group. One researcher was the moderator and the second researcher observed the discussion and took notes. All interviews will be tape recorded and written out verbatim. Afterwards, the tape records will be deleted.

